**Enrollment**								
	Eligibility screen	✓						
	Informed consent	✓						
	Medical history	✓						
	Allocation	✓						
	Randomization	✓						
**Intervention**								
	Intervention group		✓					
	Placebo group		✓					
**Assessment**s								
	Incidence of SAP^a^			✓	✓		✓	✓
	Modified Marshall score	✓		✓	✓		✓	✓
	Modified CTSI^b^	✓		✓	✓		✓	✓
	APACHE II^c^ score	✓		✓	✓		✓	✓
	C-reactive protein	✓		✓	✓		✓	✓
	IL^d^-1	✓		✓	✓		✓	✓
	IL-4	✓		✓	✓		✓	✓
	IL-6	✓		✓	✓		✓	✓
	IL-8	✓		✓	✓		✓	✓
	IL-10	✓		✓	✓		✓	✓
	TNF^e^-α	✓		✓	✓		✓	✓
	Safety outcomes	✓		✓				
	Hospitalization							✓
	Survival							✓

^a^SAP: severe acute pancreatitis.

^b^CTSI: computed tomography severity index.

^c^APACHE II: Acute Physiology and Chronic Health Evaluation II.

^d^IL: interleukin.

^e^TNF: tumor necrosis factor.

### Primary Outcomes

The primary outcome of this study is the incidence of SAP, which will be calculated using the following formula:

SAP incidence (%) = (number of SAP cases/total number of patients) × 100%

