**Objective:**

This study aims to evaluate the efficacy and safety of DaXianXiong decoction in preventing AP from progressing to SAP, assessing its impact on SAP incidence, clinical severity scores, inflammation markers, and gastrointestinal function, and providing evidence for AP management.

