## Introduction

Acute pancreatitis (AP) is a common yet potentially fatal inflammatory disorder of the pancreas, characterized by severe abdominal pain, multi-organ dysfunction, and pancreatic necrosis. The global incidence of AP is approximately 30-40 cases per 100,000 people, with over 2000 fatalities annually [1]. Severe AP (SAP), which involves persistent organ failure lasting ≥48 hours, is the most life-threatening form of AP, with a mortality rate of 20%-40% despite significant advancements in treatment [2-4]. Approximately 20% of patients with AP progress to SAP, which is associated with severe complications such as organ failure, infections, and increased health care costs [1,5].

The pathophysiology of AP is characterized by premature activation of trypsin within the pancreatic acinar cells, triggering pancreatic autodigestion and leading to a systemic inflammatory response. This response results in systemic inflammatory response syndrome, which can progress to multi-organ dysfunction syndrome [6,7]. Although the treatment of AP is mainly supportive, including fluid resuscitation and organ support, there remains a lack of consensus on the optimal management protocols for fluid therapy [8,9], and strategies to promote gastrointestinal recovery remain limited [10].

In addition to conventional Western treatments, Chinese herbal medicines have gained attention for their potential in managing AP. Chinese herbal medicines are known for their ability to target multiple biological pathways involved in inflammation, immune response, and organ protection, offering a broader approach compared to single-target Western therapies [11,12]. DaXianXiong decoction, a traditional herbal formula used in China for over 30 years, has been reported to improve gastrointestinal symptoms and modulate inflammation. However, its clinical efficacy in preventing the progression of AP to SAP has not been conclusively demonstrated due to the lack of robust randomized controlled trials [12-14].

In light of these challenges, there is an urgent need for high-quality studies to evaluate the efficacy and safety of DaXianXiong decoction in the treatment of AP. This study aims to assess the potential of DaXianXiong decoction in preventing the progression of AP to SAP, reducing inflammatory markers, improving gastrointestinal function, and assessing safety and complications.

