### Study Population

Patients will be enrolled from the intensive care unit in Chongqing Traditional Chinese Medicine Hospital, a grade III level A hospital in China.

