### Inclusion Criteria

We will select patients based on the following inclusion criteria:

Presence of AP as confirmed using the revised Atlanta classification [15]Aged 18-75 yearsTime of illness onset under 24 hours

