### Outcome Measures

The outcome measures will be determined at various time points throughout the study, including baseline (T0, before treatment), 24 hours after the final treatment (T1, end point 1), 3 days after the final treatment (T2, end point 2), 7 days after the final treatment (T3, end point 3), and 28 days after the final treatment (T4, final end point). The data collection and assessment schedule are listed in Table 2.

**Table 2 table2:** The data collection and assessment schedule.

Assessments		Study period				Follow-up		
		Enrollment and allocation (T0)	Intervention (48 hours)	Primary end point (T1)	T2		T3	T4

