#### Modified Marshall Score

Organ failure plays a significant role in the severity of AP. The revised Atlanta classification recommends the use of the modified Marshall scoring system as the primary tool for assessing organ failure. The modified Marshall scoring system encompasses scoring systems for respiratory, cardiovascular, and renal systems to evaluate organ dysfunction in AP [6].

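### The primary outcome does not separate organ failure that arises after randomisation from organ failure already present at T0 that persists, and eligibility does not clearly keep the latter out

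*Protocol article*

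**What the plan says.** SAP here means severe acute pancreatitis throughout.

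- **Aim** (Protocol article, Abstract, Objective): to "evaluate the efficacy and safety of DaXianXiong decoction in preventing AP from progressing to SAP".
- **Primary outcome** (Primary Outcomes): "SAP incidence (%) = (number of SAP cases/total number of patients) × 100". The formula has no condition that the organ failure be new, and its denominator is everyone.
- **Definition of SAP** (Introduction): "Severe AP (SAP), which involves persistent organ failure lasting ≥48 hours".
- **Source of patients** (Study Population): "Patients will be enrolled from the intensive care unit in Chongqing Traditional Chinese Medicine Hospital".
- **Entry** (Inclusion Criteria): "Presence of AP as confirmed using the revised Atlanta classification", with age 18 to 75 and onset less than 24 hours before. No severity grade is set.
- **Nearest exclusion** (Exclusion Criteria): serious disease of vital organs, illustrated by liver dysfunction, heart failure and cancer. Neither SAP, pancreatitis-related organ failure nor a Marshall threshold is named.
- **Organ failure tool** (Modified Marshall Score): "The revised Atlanta classification recommends the use of the modified Marshall scoring system as the primary tool for assessing organ failure". Table 2 schedules this score at T0 and at T1 to T4. It schedules the incidence of SAP at T1 to T4 only. Nothing links the T0 score to eligibility or to the primary outcome.

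**The concern.** In an intensive care unit it is foreseeable that some patients will have respiratory, circulatory or renal failure from the pancreatitis before they are randomised. For such a patient, becoming a SAP case means that existing failure did not resolve within 48 hours. For a patient without organ failure at T0, it means that failure began after entry and then lasted. These are different events, and treatment may affect them differently, but the formula adds them together.

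Two things are at stake. First, a difference, or its absence, could not be attributed to preventing new organ failure as opposed to helping existing failure resolve. Second, T0 organ failure is likely to be a strong predictor of the outcome. With 30 patients per arm, a chance difference in its frequency could noticeably shift the comparison if the analysis ignores it.

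**Working it through.** **Step 1: timing.** Onset is under 24 hours at entry and SAP needs at least 48 hours of organ failure, so nobody can already meet the SAP definition for this episode at entry. The course lasts 48 hours and T1 is 24 hours after it: 48 + 24 = about 72 hours from the start. Failure present at T0 that lasts 48 hours or more is therefore a SAP case under the formula. Failure that resolves sooner is not.

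**Step 2: dilution.** The article gives no frequency of organ failure at entry, and its sample size was set on the time for blood amylase to normalise, so it has no SAP figure to reproduce. The inputs are:

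- control risk of SAP in patients without persisting entry failure: 20%, the Introduction's general rate of progression;
- treated risk in the same patients: 10%, an assumed halving;
- *f*, the share entering with failure that persists in either arm: assumed, range 0 to 30%.

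Control risk = *f* + (1 − *f*) × 0.20. Treated risk = *f* + (1 − *f*) × 0.10.

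| *f* | Control | Treated | Apparent risk ratio | Share of control cases with failure at entry |
|---|---|---|---|---|
| 0 | 20.0% | 10.0% | 0.50 | 0% |
| 5% | 24.0% | 14.5% | 0.60 | 21% |
| 10% | 28.0% | 19.0% | 0.68 | 36% |
| 20% | 36.0% | 28.0% | 0.78 | 56% |
| 30% | 44.0% | 37.0% | 0.84 | 68% |

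Softer variant: if 5% to 30% enter with failure but only half of it persists, in both arms alike, the ratio runs from (0.025 + 0.095)/(0.025 + 0.190) = 0.56 to (0.15 + 0.07)/(0.15 + 0.14) = 0.76.

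**Step 3: when dilution vanishes.** Suppose 20% have failure at T0, persisting in 50% on control and 25% on treatment, and the other 80% develop SAP at 12.5% and 6.25%.

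- Control: 0.20 × 0.50 + 0.80 × 0.125 = 0.20.
- Treated: 0.20 × 0.25 + 0.80 × 0.0625 = 0.10.

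The ratio is 0.50. Dilution thus depends on treatment doing less for existing failure than for new failure.

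**Step 4: chance imbalance.** Take the number with T0 organ failure in each arm as an independent Binomial(30, *p*). The probability that the arms differ by 3 or more patients (3/30 = 10 percentage points) is 0.275, 0.417 and 0.481 for *p* = 0.1, 0.2 and 0.3. If all of that failure persisted, an imbalance of 3 patients would by itself move the SAP difference by up to 10 points, as much as the assumed effect of 20% against 10%.

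**The case against.** The strongest reply is that the formula is correct as it stands. By the document's own definition every SAP case becomes one after enrolment, so calling it incidence over all patients is accurate, and the missing T0 tick for SAP in Table 2 simply follows from the 48-hour rule. The Discussion (Expected Findings) also speaks of patients whose pancreatitis already includes organ failure going on to SAP, so moving from early to persistent failure falls within what the authors mean by progression. This stands. A reader might infer that patients who already have SAP are enrolled and counted, or that the outcome does not measure prevention of progression at all. The documents support neither reading.

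Nor is there support for saying that the entry cases are fixed before dosing and cannot be prevented. That assumes entry failure always persists and is untouched by treatment, and Step 3 shows that the dilution disappears without it.

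It is also fair that the imbalance figures would hold for any binary baseline factor of that frequency. They describe chance variation, which the significance test allows for, and not systematic bias between the arms. Finally, the exclusion for serious vital-organ disease is open-ended and could be read to remove some of these patients. Its examples read as pre-existing conditions, but the text is ambiguous.

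What the reply does not answer is that the two kinds of event are indistinguishable in the result, although the score that would separate them is already scheduled at T0.

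**Conclusion.** The point holds in a limited form. Eligibility does not clearly exclude pancreatitis-related organ failure at entry, and the primary outcome combines onset of new failure with persistence of existing failure. It still measures progression to SAP as the authors use the term, but it cannot show which component the decoction changed.

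The possible dilution, from a true risk ratio of 0.50 to about 0.60 to 0.84, is illustrative. It rests on an assumed 5% to 30% entering with failure that persists in either arm, a 20% background rate taken from pancreatitis in general, and an assumed halving. It is zero if treatment acts equally on existing failure. The imbalance affects precision and interpretation in a 60-patient trial and does not bias the comparison systematically.

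**What to change.** 1. Keep SAP in all randomised patients as the primary analysis.
2. State how SAP is derived from the serial modified Marshall scores, including how failure present at T0 is handled and how a duration of 48 hours is established.
3. Stratify or adjust the primary comparison by organ failure at T0.
4. Add a supportive analysis of new persistent organ failure among patients without organ failure at T0, and report patients with T0 organ failure separately.
5. Clarify whether the vital-organ exclusion was meant to cover organ failure due to the pancreatitis.
6. Limit any conclusion that progression was prevented to what these separate results support.

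The Results section says the data have been collected and are being analysed, so a new entry exclusion is no longer useful. Replacing the primary denominator now would be a change of primary outcome after data collection, which is why the restricted analysis should be supportive only. These definitions should be set before any unblinded comparison, or labelled post hoc.

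The cost is small, because the T0 score is already scheduled and only a little analysis is added. The supportive subset will be smaller and imprecise. If 10% to 30% have T0 organ failure, 27 to 21 patients per arm remain, and power for 20% against 10% is about 17% to 14%, compared with about 19% at 30 per arm. The change improves interpretation and does not remedy the low power.

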### Secondary Outcomes

#### Modified Computed Tomography Severity Index

According to the analysis of the area under the curve, the modified computed tomography severity index demonstrates the highest accuracy in predicting SAP. It is a simpler and more accurate scoring tool, showing a stronger statistical correlation with factors such as length of hospital stay, development of infection, organ failure, and mortality [17,18]. It will be determined using the following formula:

Computed tomography severity index = (original score – current score)/original score × 100%

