#### APACHE II Score

The APACHE II (Acute Physiology and Chronic Health Evaluation II) scoring system has high sensitivity and exhibits a negative predictive value in predicting pancreatic necrosis and organ failure. This makes it an ideal prognostic tool for assessing the severity of AP and in guiding clinical decision-making, particularly in resource-limited countries [19]. It is determined using the following formula:

APACHE II = (original score – current score)/original score × 100%

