#### Levels of Inflammation Factor

The level of an inflammation factor is a surrogate marker for important clinical end point variables in AP. Multiple studies have shown that C-reactive protein is a good surrogate marker for SAP [20,21]. Additionally, interleukin (IL)–6 is superior in predicting SAP compared to other commonly used markers such as erythrocyte sedimentation rate. The level of an inflammation factor can be determined using the following formula [22]:

Inflammation factor = (original figure – current figure)/original figure × 100%

We will also use IL-1, IL-4, IL-8, and IL-10 to investigate the potential targets of DaXianXiong decoction. In pancreatitis, cytokines such as tumor necrosis factor–α secreted by acinar cells and damage-associated molecular patterns play a major role in activating immune cells such as neutrophils and macrophages. This process leads to increased pancreatic damage, systemic inflammation, and the development of SAP [8,23].

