### Sample Size

We will use preset sample sizes (*n*) determined using the following formula:

Where *μ*_1_ and *μ_2_* are the means of the intervention and placebo groups, respectively, and *σ* is the SD. The study aims to maintain the type I error probability (*α*) to <5% and the type II error probability (*β*) to <10%, with the *α* at .05 and the *β* at .1. To determine the sample size, we referred to literature reports in Chinese [24] on the use of DaXianXiong decoction for the treatment of AP. We used the time blood amylase took to return to normal levels to determine the clinical efficacy of the decoction. We fixed the total sample size for the study at 60. We allocated 30 patients to the intervention group and the remaining 30 to the placebo group.

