### Data Analysis

Data analyses will be performed using SPSS 24.0 software. Continuous variables with a normal distribution will be analyzed using Student *t* test, while nonnormally distributed variables will be analyzed using the Wilcoxon rank sum test. Categorical variables will be analyzed using Pearson *χ*^2^ test. Continuous variables will be presented as mean (SD), while categorical variables will be presented as percentages. Values with *P* values ≤.05 will be considered statistically significant, and all tests will be 2-sided.

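### Modified CTSI, APACHE II and inflammatory markers are fixed as unadjusted percentage change from baseline: undefined at a zero baseline, asymmetric, and often less powerful than a baseline-adjusted analysis

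*Protocol article*

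**What the plan says.** Under Secondary Outcomes, the protocol article gives three formulas of the same form:

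- Modified CTSI: "Computed tomography severity index = (original score – current score)/original score × 100" (per cent).
- APACHE II: "APACHE II = (original score – current score)/original score × 100" (per cent).
- CRP, interleukins and TNF-α: "Inflammation factor = (original figure – current figure)/original figure × 100" (per cent).

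The modified Marshall score has no such formula. Data Analysis assigns normally distributed continuous variables to Student's t test, while "nonnormally distributed variables will be analyzed using the Wilcoxon rank sum test"; "all tests will be 2-sided". It names no baseline covariate, and it presents continuous variables as mean and SD without exempting skewed ones. Table 2 schedules all these measures at T0 and again at T1 to T4. On size, Sample Size states: "We allocated 30 patients to the intervention group and the remaining 30 to the placebo group".

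**The concern.** Three things follow from dividing each patient's change by that patient's own baseline.

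1. A baseline of 0 gives no value. Inclusion Criteria set no minimum score and admit patients within 24 hours of onset, so 0 is not ruled out. A patient who starts at CTSI 0 and worsens shows the progression that the trial aims to prevent, yet has no computable outcome. That sits badly with the intention-to-treat aim in the sections on withdrawals and dropouts.
2. The scale treats improvement and worsening unequally, so a mean and SD can be driven by a few patients with small denominators.
3. The T0 value serves only as a denominator. Its prognostic information is not otherwise used, although it is already collected and the trial is small.

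**Working it through.** **Inputs from the document.** The three formulas, the unadjusted two-sided tests, α = 0.05, and 30 patients per arm.

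**Inputs assumed.** The document gives no SD, baseline distribution or correlation for these outcomes. Assumed here are a true effect of 0.6 SD, a baseline-to-follow-up correlation r of 0.3 to 0.7, and the score distributions named below.

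**The plan's own figure.** The 60 patients rest on time to normal blood amylase, with no means or SD given, so the number cannot be reproduced and says nothing about power for these outcomes. Solved backwards, 30 per arm at 90% power implies d = (1.960 + 1.282) × √(2/30) = 0.837. The present point does not depend on it.

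**Step 1, zero baseline.** (0 − y)/0 is undefined for every y. Expected zeros among 60 patients, from rounded normal scores floored at 0:

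| Assumed baseline | Expected zeros of 60 |
|---|---|
| APACHE II-like, mean 8, SD 4 | about 1.9 |
| APACHE II-like, mean 12, SD 5 | 0.6 |
| APACHE II-like, mean 12, SD 4 | 0.1 |
| CTSI-like, even values 0–10, mean 4, SD 2 | about 4 |

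**Step 2, asymmetry.** A fall from 8 to 2 scores (8 − 2)/8 = +75%. A rise from 2 to 8 scores (2 − 8)/2 = −300%. The mean raw change of these two patients is 0, but the mean percentage is (75 − 300)/2 = −112.5%.

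**Step 3, power under an additive effect.** As an analytic guide, power ≈ Φ(0.6 × √15 / f − 1.96), where f is 1 for the follow-up score, √(2(1 − r)) for raw change and √(1 − r²) for ANCOVA. At r = 0.5 this gives 64%, 64% and 77%. Percentage change itself needs simulation (30 per arm, 2,000–3,000 trials per setting; zero baselines left out of percentage change and kept in ANCOVA). Results at r = 0.5:

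| Outcome | t test, % change | Wilcoxon, % change | ANCOVA |
|---|---|---|---|
| APACHE II-like (mean 8, SD 4) | 44–49% | 61–64% | 72% |
| CTSI-like, integer values (mean 4, SD 2) | 51% | 62% | 74% |
| CTSI-like, even values only | 52% | 55% | 68% |
| Log-normal marker (ANCOVA on log scale) | 44–53% | 59–61% | 74% |

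Ranges come from separate runs. A further independent simulation gave 44–50%, 60–63% and 74–76%. Over r = 0.3 to 0.7 (APACHE II-like, even-valued CTSI-like and marker settings), ANCOVA gains about 12–38 points over the t test and about 5–20 over Wilcoxon. Under no effect, rejection rates were 4.3–4.9% for all methods.

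**Step 4, power under a proportional effect.** This is the case most favourable to percentage change. With log-normal data in four settings, the t test on percentage change reached 70–72%, Wilcoxon 70–80%, raw-scale ANCOVA 42–62% and log-scale ANCOVA 72–81%. Setting by setting, log-scale ANCOVA gained only 1–2 points over Wilcoxon. For an APACHE II-like score with a 25% proportional reduction, percentage change reached 73–74%, raw-scale ANCOVA 66% and ANCOVA on log(score + 1) 76%.

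**The case against.** The strongest reply is that the power loss is an assumption rather than a fact. An additive shift favours ANCOVA. Step 4 shows the ranking reverse for raw-scale ANCOVA when the effect is proportional. This stands, and it limits both the claim and the remedy.

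The t test is also not the fairest comparator. A measure bounded above and unbounded below is likely to be judged nonnormal, and the plan then uses Wilcoxon, so the smaller gain is the relevant one. Extreme values still distort the reported mean and SD, but not the rank test.

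A reader might infer that patients will certainly be lost. The document does not support that. Study Population recruits from intensive care, where zero APACHE II scores may be rare. The article never says that undefined cases are excluded; it is silent. For CRP and cytokines, values near or below the detection limit are the likelier problem. Since baseline assessment precedes allocation, dropping zero baselines would narrow the analysed population rather than by itself favour an arm.

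A reader might also infer invalid tests or a threat to the main result. Neither follows. Null rejection is close to 5%, and SAP incidence, the primary outcome in the body of the article, is untouched. The Abstract lists these scores and the inflammation factor among the primary outcomes, but that is a separate inconsistency.

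Finally, covariate adjustment is often left to a statistical analysis plan. That would answer a silent protocol. Here the percentage formulas and the unadjusted tests are stated.

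**Conclusion.** The point holds as a defect in how three secondary outcomes are defined and compared, and it should be corrected. The missing zero-baseline rule and the asymmetry follow from the formula and need no assumptions; how often a zero occurs does. The loss of power is conditional. With an additive 0.6 SD effect and r = 0.5, ANCOVA gains roughly 8–15 points over Wilcoxon and more over the t test. With a proportional effect the gain over Wilcoxon is a point or two on the log scale, and raw-scale ANCOVA can lose. A general statement that percentage change always wastes power would go beyond the evidence.

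**What to change.** - Make the main analysis of these secondary outcomes the follow-up value with its own baseline as covariate, by ANCOVA at each visit or one mixed model over T1 to T4.
- Analyse CRP and cytokines on the log scale, with a stated value for results below the detection limit.
- Analyse CTSI and APACHE II as the score with baseline as covariate, and add ANCOVA on log(score + 1) or a rank-based ANCOVA as sensitivity analysis, since raw-scale ANCOVA can do worse under a proportional effect.
- Report adjusted differences or ratios with 95% confidence intervals, and median (IQR) for skewed variables. Keep percentage change as descriptive only.

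Baseline is already collected, so no new data are needed, but this is more than a wording change. Results states that data are collected and under analysis, and Modification of the Protocol requires consent of the project leader and supervisor and ethics committee approval. Record the change in a dated amendment before unblinding. If that is no longer possible, report the adjusted analysis beside the planned one and label it post hoc. The cost is the amendment and a small amount of extra analysis.
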